### Statistical analysis

All quantitative analyses will be performed in R. Baseline characteristics will be summarized using appropriate descriptive statistics. Continuous variables will be presented as means and standard deviations or medians and interquartile ranges depending on distribution, and categorical variables as counts and percentages. Baseline characteristics will be summarized at both participant and cluster levels to assess imbalance that may be important in a trial with few clusters.

The principal quantitative analysis will follow the intention-to-treat principle and use marginal repeated-measures models to account for repeated measurements within participants and clustering by nursing home. The planned primary model is a nested generalized estimating equations (GEE) model with nursing home specified as the top-level cluster and participant nested within nursing home, using an exchangeable working correlation structure. Because only six randomized clusters are available, GEE results will be treated as model-based estimates rather than as definitive inferential tests. The primary GEE variance estimate will use a bias-corrected sandwich approach suitable for small samples, prioritizing the Mancl–DeRouen correction where implementable and using Fay–Graubard or related small-sample corrections as sensitivity checks (34, 35). Analyses will be implemented in R using packages capable of modified GEE variance estimation, such as geesmv where appropriate (36). Models will include fixed effects for group, time, and the group-by-time interaction, with the interaction terms at 6 weeks and 12 weeks treated as the main estimates of between-group change over time.

The primary GEE analysis is conducted under a working missing-completely-at-random (MCAR) assumption, which is the standard requirement for consistency of GEE estimators in the absence of additional weighting. The plausibility of MCAR will be examined by comparing baseline characteristics of participants with and without complete follow-up. To address potential departures from MCAR, sensitivity analyses will use (i) multiple imputation by chained equations under a missing-at-random (MAR) assumption with auxiliary baseline variables, and (ii) inverse-probability-of-attrition-weighted GEE. Mixed-effects models will be considered as supportive analyses only, given known instability of likelihood-based variance components with fewer than approximately 10 clusters per arm.

Given the small number of randomized clusters, conventional *p* values from GEE models may be unstable. The analysis will therefore emphasize effect estimates, 95% confidence intervals, direction and consistency of change, and clinical plausibility rather than dichotomous hypothesis testing. Cluster-level change-score summaries will be prioritized as the main robustness analysis, and randomization/permutation-based checks will be conducted over the retained covariate-constrained allocation set where feasible. These checks will be interpreted descriptively because the number of possible clusters and allocations is very small. If model convergence or standard-error estimation is unstable, non-parametric descriptive comparisons and cluster-level summaries will be emphasized over model-based *p* values. This approach follows recommendations that cluster-level methods and small-sample corrections should be considered when CRTs include few clusters, while recognizing that no analytic correction can fully overcome the design limitation of six randomized clusters (37).

Prespecified covariates may include age, sex, educational level, marital status, dementia severity category, years since diagnosis, length of nursing-home stay, baseline outcome value, baseline medication exposure, social interaction level, weekly participation in other therapeutic activities, and attachment-related or caregiving-history indicators where available. Covariate adjustment will be parsimonious because of the limited number of clusters and events, and adjusted analyses will be interpreted as sensitivity analyses rather than as a way to remove all baseline imbalance. Missing data patterns will be summarized by group and time point.

Per-protocol analysis will be conducted as a sensitivity analysis among intervention participants who accept the doll and attend at least six of the eight planned introductory sessions (>=75% adherence). The 75% threshold was selected *a priori* on the basis that the dose–response relationship of doll therapy is not established and 75% adherence is a conventional cut-off used in non-pharmacological dementia-care trials to define adequate exposure. Engagement-informed exploratory analyses may describe whether greater exposure or more positive interaction with the doll is associated with more favorable changes in NPI-12, Barthel Index, or medication-related outcomes within the intervention arm. These analyses will be hypothesis-generating only.

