The conceptual rationale for the intervention is informed primarily by attachment theory. Dementia-related losses in memory, orientation, and social familiarity may intensify needs for security, soothing, and emotional regulation. Within this framework, a doll may function as a symbolic attachment object and support caregiving identity, comfort, and meaningful engagement for some residents (13, 14). The hypothesized causal chain from doll therapy to medication-related outcomes therefore involves two distinct steps: (i) a behavioral step in which attachment-informed engagement reduces dementia-related distress behaviors as captured by validated instruments such as the Neuropsychiatric Inventory-12 (NPI-12), and (ii) a prescriber response step in which clinicians and medication-review processes translate behavioral stabilization into reduced or stable psychotropic prescribing. The current pilot protocol does not directly measure attachment processes or formally test mediation; attachment-related mechanisms are inferred theoretically, while engagement records and qualitative interviews provide only indirect contextual evidence. Because the second step depends on prescriber behavior and institutional policy rather than on the intervention itself, any medication-related change observed in this trial will be interpreted alongside more proximal outcomes, particularly NPI-12, Barthel Index, and structured engagement records. In the Chinese care context, this rationale also needs to be considered alongside local cultural understandings of ageing, family caregiving, dignity, institutional care, and the coexistence of biomedical treatment and traditional Chinese medicine in routine dementia care (5, 15).

Doll therapy also remains ethically and culturally sensitive. Concerns have been raised about infantilization, deception, over-attachment, and respect for autonomy and dignity, especially if the intervention is imposed, poorly explained, or treated as a substitute for relational care (16, 17). Acceptability may vary according to residents’ prior life experiences, family expectations, staff attitudes, gendered caregiving histories, cultural beliefs about dolls and old age, and degree of cognitive impairment. These issues are central to the present protocol rather than peripheral implementation details.

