3/Day 5	Love Me and Hug Me	Invite holding, touching, or comforting the doll according to preference; stop if refusal, fear, or agitation occurs.	Attachment theory; emotional regulation
4/Day 7	Listen to Me	Use open conversation or reminiscence prompts related to caregiving, family, or daily life; avoid corrective or deceptive language.	Attachment theory; reminiscence and self-identity
5/Day 9	Lovely Family	Support simple doll-care activities such as dressing or grooming; observe fine motor engagement and distress signals.	Attachment theory; purposeful activity
6/Day 11	Enjoying the Moment	Use music, storytelling, or calm shared activity with the doll; document duration and quality of interaction.	Attachment theory; positive affect and engagement
7/Day 13	Raising Babies	Simulate nurturing tasks only when welcomed by the resident; monitor possessiveness, conflict, or interference with care.	Attachment theory; caregiving role continuity
8/Day 15	Better Tomorrow	Review preferred activities, consolidate comfort routines, and plan safe continued access during routine care.	Attachment theory; continuity and closure

Sessions are scheduled on days 1, 3, 5, 7, 9, 11, 13, and 15. Each session lasts approximately 20–30 min and is adjusted to the resident’s attention, fatigue, and emotional response. Deviations from the planned schedule due to acute illness, fatigue, or staffing constraints will be documented.

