### Safety monitoring and harms

Doll therapy is considered a low-risk psychosocial intervention, but potential adverse responses include distress, agitation, possessiveness, interpersonal conflict, family concern, worsening confusion, or over-attachment to the doll. Each participant in the intervention arm will be assigned an individual doll, and dolls will not be shared between residents. Dolls will be cleaned according to each facility’s infection-control procedures while preserving participants’ sense of ownership and comfort.

Resident assent will be monitored throughout the study. Refusal or dissent may be verbal, such as saying no or asking staff to remove the doll, or non-verbal, such as pushing the doll away, turning away repeatedly, crying, showing fear, increased agitation, or clear discomfort. If a resident shows refusal or distress, staff will stop the interaction for that occasion, remove or set aside the doll respectfully, provide reassurance, and record the event. Reintroduction may be attempted only when the resident is calm and willing. Two consecutive sessions with refusal or significant distress will trigger an individualized review by the site clinician; three consecutive refusals or any persistent doll-related distress will result in discontinuation of doll exposure for that participant, with the resident retained in the intention-to-treat analysis.

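### The per-protocol set is selected on post-randomisation behaviour in the intervention arm only, with no named comparator, so it cannot act as a sensitivity analysis of the intention-to-treat result

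*Protocol article*

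**What the plan says.** The Statistical analysis section makes intention-to-treat the main approach: "The principal quantitative analysis will follow the intention-to-treat principle". It then adds a second analysis: "Per-protocol analysis will be conducted as a sensitivity analysis". The residents it covers are described in these terms: "among intervention participants who accept the doll and attend at least six of the eight planned introductory sessions". The reason given for the cut-off is that "75% adherence is a conventional cut-off used in non-pharmacological dementia-care trials to define adequate exposure". That reason concerns exposure and does not address how selection affects the comparison. The text names no control group for this analysis, no matching restriction on controls and no adjustment for selection.

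The section on safety monitoring links exposure to reaction: "three consecutive refusals or any persistent doll-related distress will result in discontinuation of doll exposure for that participant". Such residents stay in the intention-to-treat analysis. The signs that count as non-verbal dissent include "turning away repeatedly, crying, showing fear, increased agitation, or clear discomfort".

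Two other statements bear on who ends up in the set. The note under the activity table says "Deviations from the planned schedule due to acute illness, fatigue, or staffing constraints will be documented". The Introduction says acceptability may vary with several factors, among them "gendered caregiving histories, cultural beliefs about dolls and old age, and degree of cognitive impairment".

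**The concern.** Acceptance and attendance can be observed only in homes that received the dolls. Controls who would have refused, become distressed or been too ill to attend remain in the control group, while their counterparts leave the intervention group. The two groups then differ in composition even if the package does nothing.

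The label adds to the problem. The plan avoids dichotomous testing and relies on the direction and consistency of estimates across analyses. A per-protocol estimate that agrees with a favourable intention-to-treat estimate would look like support, although part of the agreement could come from selection. The stated estimand is the package as delivered in routine care, which includes residents who decline it. The per-protocol set answers a different question, so it does not test the assumptions behind the intention-to-treat result. The protocol discusses attention confounding and positivity bias in the interviews, but never this selection.

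**Working it through.** **1. The plan's own figure.** The cut-off reproduces: 6 / 8 = 75%. The plan gives no figure for the expected size of the set.

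**2. Stopping rule against cut-off.** Inputs: eight sessions, a cut-off of six, and a stop at three consecutive refusals.
- Eight sessions give 2^8 = 256 accept/refuse patterns, of which 107 contain three refusals in a row.
- In those 107, the largest number of accepted sessions is 8 - 3 = 5, so none reaches six.
- This assumes that a refused session is not counted as attended and that the refusals fall within the eight sessions. The outcomes section lists attendance and refusal as separate indicators, so the first premise is open.
- If refused sessions do count, a resident stopped at session 5 or earlier still has at most five. One stopped at session 6, 7 or 8 could qualify on attendance and would be excluded only by the acceptance condition, which the text does not define.

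**3. Size of a possible bias with no true effect.** The document gives neither the share excluded (q) nor the correlation (rho) between the tendency to be excluded and a worse NPI-12 change. Both are assumed. If the tendency and the outcome are jointly normal, removing a share q shifts the mean of those retained, in favour of doll therapy when rho is positive, by

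bias = rho x phi(z_q) / (1 - q), in SD units.

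For q = 0.20: 0.280 / 0.80 = 0.350, times 0.3 = 0.105. For q = 0.30: 0.348 / 0.70 = 0.497, times 0.3 = 0.149.

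| Share excluded | rho = -0.3 | rho = 0 | rho = 0.1 | rho = 0.3 | rho = 0.5 |
|---|---|---|---|---|---|
| 10% | -0.06 | 0 | 0.02 | 0.06 | 0.10 |
| 20% | -0.10 | 0 | 0.03 | 0.10 | 0.17 |
| 30% | -0.15 | 0 | 0.05 | 0.15 | 0.25 |
| 40% | -0.19 | 0 | 0.06 | 0.19 | 0.32 |

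Positive values favour doll therapy. The Sample size section uses 0.5 SD as its planning difference for NPI-12, with an SD of 10-15. For 20-30% excluded and rho = 0.3, the bias is 0.105 / 0.5 = 21% to 0.149 / 0.5 = 30% of that difference. In points it runs from 0.105 x 10 = 1.0 to 0.149 x 15 = 2.2, taking the plan's SD to apply to the change as well.

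**4. Simulation check.** Six homes of 24 residents, ICC 0.05, true effect zero. The intention-to-treat difference averaged about 0.00 SD in every case. The per-protocol difference against all controls (negative means lower NPI-12 in the doll arm) averaged 0.00 at 20% excluded and rho = 0, -0.11 at 20% and 0.3, -0.15 at 30% and 0.3, and -0.25 at 30% and 0.5. This agrees with the formula.

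**5. Against sampling error.** An equal split of 142 gives 71 per arm; 20% excluded leaves about 57. The standard error of the difference before any allowance for clustering is sqrt(1/57 + 1/71) = 0.18 SD. The bias in step 3 is smaller than this, so it could not be seen in the data of this one trial.

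**The case against.** The harm is largely contained. Intention-to-treat is principal, stopped residents stay in it, and the plan names cluster-level change-score summaries as its main robustness analysis. Conclusions are weighted first to feasibility and safety. All of this stands and limits the weight of the point. The remark that analyses are hypothesis-generating comes directly after the engagement-informed analyses, and its reach to the per-protocol analysis is unclear.

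A reader might infer three stronger things that the document does not support.
- **The set is purged of poor responders.** It is not. A resident who accepts the doll, attends six sessions and worsens stays in. So, on attendance, does one stopped for distress after the introductory phase of about 15 days. Sessions can also be missed because of staffing, which says nothing about response.
- **Every resident stopped for refusal falls below six sessions.** That holds only under the two premises in step 2 of the working.
- **The contrast with controls is certainly biased towards doll therapy.** The text names no comparator; a contrast with controls is the natural reading of per-protocol, but it is inferred. Acceptance is said to vary with caregiving history, culture and cognitive impairment, so those who refuse could have a better course.

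The open comparator does not rescue the analysis. With controls, the comparison loses randomisation's protection. Without them, it cannot test a between-group estimate.

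**Conclusion.** The point holds in a limited form. The plan fixes a set chosen by post-randomisation, response-related behaviour in one arm, gives no comparator, and calls the result a sensitivity analysis. A comparison of that set with controls is not protected by randomisation.

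A bias in favour of doll therapy is the more likely direction, because distress, agitation and acute illness are the most direct routes out of the set. Neither direction nor size can be derived from the document. The figure of 0.10-0.15 SD rests on an assumed 20-30% excluded and an assumed correlation of 0.3; it vanishes at zero correlation and changes sign at a negative one. The principal analysis is unaffected. What needs correcting is how this secondary estimate is defined and what it may be used to support.

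**What to change.** In the Statistical analysis section:
- Stop describing this as a sensitivity analysis of the intention-to-treat result.
- Report adherence and the outcomes of adherent residents descriptively, or present a supplementary estimate labelled as prone to selection. In the second case, name the comparator.
- Define what accepting the doll means for this analysis, and state whether a refused session counts as attended.
- If an adherence-adjusted estimate is wanted, keep all controls and weight adherent intervention residents by the inverse probability of adherence, using a few baseline variables already collected (for example baseline NPI-12, severity, age and sex). State that it corrects measured selection only and is not a robustness check on intention-to-treat.

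The descriptive option costs a few sentences. The weighted option needs one extra model, fitted on about 71 intervention residents in three homes. Its interval will be wider, the covariate list must stay short, and reactions to the doll that baseline variables do not predict remain uncorrected.

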### Data management

Quantitative data will be recorded on standardized forms by trained personnel at each nursing home and will include demographic and clinical variables, medication records, outcome measures, co-intervention information, adverse responses, and adherence and engagement documentation. Qualitative data will include audio files, transcripts, field notes, reflexive notes, and analytic memos. Paper materials will be stored in locked cabinets, and digital files will be stored in password-protected systems with access limited to authorized study personnel.

All datasets will be de-identified before analysis using unique study identifiers. Data queries, discrepancies, and protocol deviations will be documented and resolved by the study team. Access to the final analytic dataset will be restricted to the principal investigator and approved analysts. Data cleaning and analysis decisions will be documented before unmasking group labels for the primary analysis where feasible.

## Discussion

This protocol describes an exploratory pilot and feasibility mixed-methods cluster randomized trial assessing the staff-mediated doll-therapy care package in Chinese residential dementia care. The study is designed to address several clinically and publicly relevant gaps. First, evidence for doll therapy in Chinese nursing homes remains limited despite increasing dementia burden and growing reliance on institutional long-term care. Second, the study examines medication burden together with behavioral symptoms, activities of daily living, and structured engagement, providing a broader preliminary assessment than agitation outcomes alone. Third, the qualitative component is intended to clarify how staff and family caregivers interpret doll therapy, what ethical concerns arise in practice, and what implementation conditions may support or hinder acceptability.

The cluster design is appropriate because the intervention is delivered within communal care environments where contamination would be difficult to avoid if individual residents within the same home were randomized to different conditions. At the same time, the study faces important anticipated limitations. Only six nursing homes are included, which limits statistical power, precision, stability of cluster-level estimates, and robustness of GEE variance estimation even with small-sample corrections. Baseline imbalance between groups may remain despite covariate-constrained randomization. Participant and caregiver blinding is not possible because the intervention is visible. Medication changes remain clinician-led rather than researcher-directed, so variation in prescribing may reflect physician practice, medication-review routines, acute illness, family preferences, staffing capacity, or institutional policies rather than the care package alone. The absence of an active attention control also limits attribution of any observed differences specifically to the doll rather than to increased staff attention, structured interaction, or enhanced activity exposure. The present estimand is therefore the doll-therapy care package as implemented in routine care, not the isolated effect of a doll object. To partially mitigate this attributional risk, the protocol will (i) document and report between-site variation in routine non-pharmacological activities and major co-interventions, (ii) examine exposure-response patterns using the structured engagement record within the intervention arm, and (iii) use the qualitative phase to identify whether observed changes are perceived by staff and family caregivers as specifically related to the doll, to broader caregiving interaction, or to other care-context changes; nonetheless, residual confounding by attention and activity exposure cannot be excluded in this design.

For these reasons, the findings of this trial will be interpreted cautiously and within the prespecified outcome hierarchy. The study can provide feasibility information, acceptability data, intervention-fidelity information, safety observations, preliminary effect estimates, and clinical signals, but it cannot establish definitive clinical effects. The registered medication-related outcomes will be interpreted as indirect medication-stewardship signals and contextual prescribing indicators. The NPI-12 is treated as the main proximal clinical outcome for interpretation because it provides a validated, behaviorally proximal measure of intervention response. The Barthel Index and cognitive enhancer use will be reported as secondary clinical outcomes. The traditional Chinese medicine score will be treated as a contextual descriptor because it is study-specific and not externally validated. Maintaining these distinctions between feasibility outcomes, the registered medication outcome, the proximal NPI-12 clinical signal, secondary clinical outcomes, and exploratory contextual measures is essential for preventing overinterpretation, particularly in a small-cluster pragmatic pilot trial.

The ethical and cultural dimensions of doll therapy are also central to this protocol. Doll therapy may be comforting and meaningful for some residents but inappropriate or distressing for others. Implementation must therefore preserve dignity and autonomy, avoid coercion and infantilizing language, respect resident assent and dissent, and include family communication and staff training. The qualitative phase will help determine whether the intervention is acceptable in Chinese residential care, how staff and families understand its meaning, and how safeguards may need to be adapted in future studies. Because qualitative interviews are limited to staff and family caregivers from intervention homes, the analysis may overrepresent participants exposed to the intervention and may be vulnerable to positivity bias. The interview guide and analysis will therefore actively seek accounts of neutral responses, distress, refusal, family concern, staff burden, and alternative explanations for observed change, but comparative qualitative interpretation with control-site staff will remain beyond the scope of this pilot protocol.

Despite these constraints, the study has potential relevance for ageing and public health. Safer non-pharmacological approaches to dementia care are needed in residential settings where psychotropic medications remain common and staffing pressures are substantial. If doll therapy proves feasible, acceptable, safe, and associated with favorable preliminary signals when delivered with staff training, ethical safeguards, fidelity monitoring, and family communication, it may offer a practical and low-cost addition to person-centered nursing-home care in rapidly ageing settings. The results will also provide methodological information for a future adequately powered cluster randomized trial with stronger control conditions, such as a structured social-interaction attention-control arm, a larger number of randomized clusters, and more precise cluster-level inference.

